##### Evaluation of birth attendants’ perceptions and learning

At each quarterly seminar, health providers will be asked to fill in two anonymous questionnaires:a Likert-scale evaluation of their experiences and perceptions of the intervention (after attendance of seminars) and a knowledge test (before and after attendance at seminars) (Figure 3). Participants’ perceptions, return rates, and learning over time will be followed using unique participant numbers. As no allowances are paid, attendance and return rates are considered indicators of interest and motivation of using the intervention, which will supplement the qualitative evaluation described below. The knowledge test will focus on key aspects of intrapartum care and will be developed and validated based on a preliminary version from the PartoMa pilot study [23].

##### Qualitative evaluation

As described separately, birth attendants, women giving birth, and hospital leadership will be engaged with different qualitative methods to facilitate a series of task-based investigations [32]. This includes an examination of the barriers and facilitators of the intervention through observations and individual interviews and unpacking collective experiences and perspectives on the strengths and limitations of the PartoMa intervention through FGDs. Together, these investigations will help build a comprehensive understanding of intervention impact and value (key to ‘value for money’) as well as scalability and replicability analyses [56].

##### Evaluation of cost-effectiveness

A pragmatic cost-effectiveness analysis will be conducted from a health-care system and societal perspective, considering incremental costs and effects related to the intervention. Cost data will be collected for both co-creation and implementation. Costs will relate to transport, time, commodities for training, and running and capital costs for training. Data will be collected by participants’ questionnaires and original receipts for direct and indirect costs, as well as daily reports on the activities of facilitators, trainers, and experts throughout co-creation and implementation. Fixed hourly rates based on national salary scales will be used to calculate costs per hour. Capital and running costs per facility and per health worker for both co-creation and implementation will be assessed. All costs will be adjusted by fixed-time exchange rates and purchasing power parity.

Effects will be measured in natural units related to the primary outcome of perinatal deaths (stillbirths with positive foetal heart on admission and pre-discharge neonatal mortality during the first 7 days among inborn babies weighing ≥1000 g) as well as to Apgar score <7. Incremental cost-effectiveness ratios (ICERs) will be calculated separately for stillbirths, neonatal mortality, and Apgar score <7. A discount rate of 3% will be applied to both costs and effect. Changes in stillbirths and neonatal deaths can be transformed into Disability-Adjusted Life Years’ (DALY’s) of a birth cohort by construction of a Markov model to estimate DALYs lost or averted in a lifetime perspective [57]. Finally, ICERs will be calculated using a life-time perspective due to stillbirth and neonatal death for: *i)* natural unit effectiveness measures listed above; and *ii)* modelled DALYs lost or averted [58,59]. Sub-group analysis will be conducted for each of the three facility clusters and for the mode of birth (vaginal versus CS). Base case of costs and effect will be explored in univariate sensitivity analysis, including variation in costs and effects between the five study sites. The non-parametric bootstrap method can be used to estimate sampling distributions of ICER and subsequently compute cost-effectiveness acceptability curves across a range of cost-effectiveness thresholds [57].

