				**Health system outcomes**
	**Health providers’ perceptions**			**Cost-effectiveness** (incremental costs and effects related to the intervention, related to maternal complications, intra-hospital perinatal deaths, Apgar score <7 and potentially avoidable caesarean sections)
	Access to the intervention during clinical work Participation rates during PartoMa seminars Perceptions of the intervention’s relevance, effects and limitations			

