##### Evaluation of direct health outcomes

Our primary direct health outcomes are perinatal survival (stillbirths with positive foetal heart upon admission and pre-discharge neonatal mortality during the first seven days among inborn babies weighing ≥1000 g) and potentially avoidable CSs (by criterion-based case file review of care preceding surgery). Our secondary direct health outcomes include additional perinatal indicators (perinatal deaths divided into 1000–1999 g and ≥2000 g, first 24 hours pre-discharge neonatal mortality, Apgar score <7, admission to neonatal intensive care unit), maternal indicators (death, postpartum haemorrhage, uterine rupture, postpartum hysterectomy), and mode of birth (spontaneous vaginal birth, vacuum extraction, CS). In addition, background characteristics will be recorded for all women (age, parity, previous perinatal death, date and time of admission and birth, and birthweight). Sociodemographic indicators such as marital, economic, and educational status are not available in birth registries.

Birth outcomes and mode of birth will be prospectively measured from baseline and until nine months after the PartoMa intervention is implemented in the last facility. Thus, data collection will be ongoing for 18 months (Figure 3). Data will be gathered twice a week on each of the five study sites, primarily from the intrapartum birth register. Key indicators will be cross-checked with the antenatal, surgical, neonatal and postnatal wards registers and with the death certificate counter book. For each study site, data will be double entered every fifth week to ensure that the accuracy of data retrieval remains above 95%. Women referred to the study sites prior to birth from non-study health facilities will be included, but their clinical care prior to admission will not be possible to assess. When referrals occur from one to another study site, data will be recorded on where the woman gave birth. Babies referred postpartum for intensive care will be recorded at the facility where the woman gave birth (Table 1).

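### The cost-effectiveness subgroup by mode of birth conditions on an outcome the intervention is meant to change, and the listed costs are narrower than the stated perspective

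*Protocol article*

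**What the plan says.** All references are to the Protocol article.

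- **Subgroups.** Evaluation of cost-effectiveness: "Sub-group analysis will be conducted for each of the three facility clusters and for the mode of birth (vaginal versus CS").
- **Status of mode of birth.** Evaluation of direct health outcomes lists among the secondary outcomes "mode of birth (spontaneous vaginal birth, vacuum extraction, CS"), and among the primary outcomes "potentially avoidable CSs (by criterion-based case file review of care preceding surgery").
- **Perspective.** The economic analysis is to be "conducted from a health-care system and societal perspective, considering incremental costs and effects related to the intervention".
- **Costs.** "Cost data will be collected for both co-creation and implementation". The items are then listed: "Costs will relate to transport, time, commodities for training, and running and capital costs for training". The sources named are participant questionnaires, receipts (for direct and indirect costs) and activity reports of facilitators, trainers and experts.
- **Effects.** ICERs are planned for stillbirths, neonatal mortality and Apgar score below 7, with modelled DALYs in addition. Table 1, under Health system outcomes, describes cost-effectiveness more widely, as "related to maternal complications, intra-hospital perinatal deaths, Apgar score <7 and potentially avoidable caesarean sections".

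**The concern.** A subgroup should be defined by something the intervention cannot alter. This intervention aims, among other things, to reduce avoidable CSs. If it succeeds, some women who would have had a CS give birth vaginally, and the CS group that remains is a different, probably sicker, mix. A change in mortality within either group then combines any real effect with this regrouping. The better the intervention works on avoidable CSs, the more the subgroup results can mislead.

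The second issue is labelling and consistency. A health-system and societal ICER would normally reflect changes in the cost of care and in household payments. The listed items and sources describe the cost of producing and delivering the programme. Avoidable CS, a primary outcome, is named in Table 1 but has no ICER and no listed cost in the text.

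Cost-effectiveness is part of the overall study objective, and the article says positive results may support adoption by the government. A reader comparing this with other investments needs to know which costs are in the ratio.

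**Working it through.** The article gives no ICER or subgroup figure to reproduce, so part 1 is an illustration on assumed inputs and part 2 a comparison of the text.

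**1. Regrouping with no true effect**

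The article does not give the sites' CS rate, the risk by mode of birth or the expected shift. Assumed, per 1,000 births:
- 250 CSs with 10 deaths and 750 vaginal births with 14 deaths (24 deaths in all);
- *m* CSs are averted, in women whose risk is *r* = 10 per 1,000 by either route.

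Formulas: CS mortality after = (10 − *mr*) / (250 − *m*); vaginal mortality after = (14 + *mr*) / (750 + *m*).

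| | Before | *m* = 20 | *m* = 30 |
|---|---|---|---|
| CS | 10/250 = 40.0 per 1,000 | 9.8/230 = 42.6 (+6.5%) | 9.7/220 = 44.1 (+10.2%) |
| Vaginal | 14/750 = 18.7 per 1,000 | 14.2/770 = 18.4 (−1.2%) | 14.3/780 = 18.3 (−1.8%) |
| All births | 24/1,000 | 24/1,000 | 24/1,000 |

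Nobody's risk has changed, yet the CS subgroup shows excess deaths and the vaginal subgroup shows deaths averted. The direction depends on who moves: CS mortality rises when the women moved have a risk below the CS average, and vaginal mortality falls when their risk is below the vaginal average.

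A wider set of 15 assumed scenarios used CS rates of 15–35%, 1–5 percentage points of births moving from CS to vaginal birth, and death risks of 0.5–1.5% for low-risk CS, 3–4% for high-risk CS and 1.5% for vaginal birth. The apparent relative risk was 1.016–1.202 in CS and 0.952–1.000 in vaginal births. The overall relative risk was 1.000 in every scenario.

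**2. Perspective, costs and effects side by side**

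| | Evaluation of cost-effectiveness | Elsewhere in the article |
|---|---|---|
| Perspective | Health-care system and societal | – |
| Costs | Co-creation and training items only; none named for CS, neonatal admission, maternal complications or household payments | Study setting: at the three regional referral hospitals women pay 11–32 USD for vaginal birth and 22–87 USD for CS |
| Effects with an ICER | Stillbirth, neonatal death, Apgar <7, DALYs | Table 1 adds maternal complications and potentially avoidable CSs |

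The fees show that one societal cost differs by mode of birth at three of the five sites. Averted CSs would lower the incremental cost. Other changes in care use, such as neonatal admissions, could raise or lower it. The article gives no unit costs, so the net effect cannot be calculated.

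**The case against.** **The main ICERs are untouched by the subgroup fault.** A reader might infer that all the ICERs are biased. The document does not support that: the ICERs for stillbirth, neonatal death, Apgar score and DALYs are not split by mode of birth, and in the illustration the overall result stays at the truth. This objection stands.

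**The cluster subgroups are defensible.** A reader might infer that ICERs by roll-out cluster are bare before-after contrasts without controls. Clusters are fixed before exposure. When the first cluster starts, the other two are still unexposed, and when the second starts, the third is. Data analyses also plans mixed models with facility-specific deviations and adjustment for seasonality. Between-site comparison serves the stated interest in transferability. This stands as a reason to keep them, labelled exploratory.

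**The cost list may not be complete.** The text does not say that only these costs count. It mentions indirect costs, Table 1 links incremental costs to complications and avoidable CSs, and user fee structure is among its data items. Itemised unit costs are commonly left to a fuller economic plan. This stands in part: omission of care costs cannot be proved. But the named sources are as narrow as the list, and the claimed perspective and the Table 1 scope remain unmatched by the section that specifies the analysis.

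**The mode-of-birth split might be meant as description.** The article does not say so. It places the split among the subgroup analyses of the cost-effectiveness evaluation.

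**Conclusion.** The point holds in two limited parts.

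1. ICERs by mode of birth condition on an outcome of the intervention and can show false harm or benefit. In the main illustration the spurious change is about +6.5% to +10% in CS mortality and −1% to −2% in vaginal mortality. These sizes rest wholly on assumed rates and risks; the mechanism does not. It needs only that the intervention changes who has a CS and that those women differ in risk from the groups they leave and join.
2. The stated perspective is wider than the costs and sources listed, and Table 1 names effects for which the text plans no ICER. This is a mismatch to be reconciled. The size and direction of any effect on the headline ICER cannot be fixed from the document.

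A reader might also be tempted to put a dollar figure on the missing costs by applying the quoted fees to all births at the five sites. The document does not support this: the fees are those of the three regional referral hospitals, and neither the CS rate nor the number averted is given.

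The primary effectiveness comparison is not affected.

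**What to change.** - **Mode of birth.** Drop the ICERs by mode of birth, or report outcomes by mode as description only, with no ICER. If a subgroup is wanted, use one fixed before exposure, such as regional versus district hospital. Cost: one subgroup table.
- **Clusters.** Keep the cluster ICERs and label them exploratory. Cost: wording.
- **Perspective.** Choose one of two routes. Either restate the perspective as programme (intervention) cost, which needs wording only, or add care costs by applying unit costs to the counts of CS, neonatal admission and maternal complications that the trial already collects. The second route takes modest extra costing work, because the article does not show that hospital unit costs exist. Do not add user fees on top of the resource cost of the same procedure: the fee is a transfer towards that cost and would be counted twice.
- **Effects.** Reconcile Table 1 with the effect list in Evaluation of cost-effectiveness: either plan ICERs for maternal complications and potentially avoidable CSs or remove them from Table 1. If avoidable CS is kept, note that it is audited only in the three baseline months and the 7th to 9th implementation months.

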#### IV. An enabling CPG development and implementation model

Based on the results of specific objectives I–III and findings from the Zanzibar pilot study, opportunities, and barriers in co-creating, implementing, and upscaling CPGs and training will be analysed. Thereby, the aim is to develop a framework for co-creating and up-scaling context-tailored CPGs and associated implementation strategies [22].

### Power calculation

We applied CCBRT’s routinely collected data for overall births and stillbirths in the five study sites from January to August 2020 (i.e. with the embedded influence of the newly introduced user fee and the COVID-19-pandemic). Based on the newest epidemiological measures from Tanzania (2012), we then set the premise that approximately 50% of stillbirths occurred intrahospital, and, conservatively, that pre-discharge neonatal mortality would be in the same range (i.e. half of overall neonatal mortality) [60]. For each maternity unit, we then calculated the average number of intrahospital perinatal deaths during 3 months, which comprises a block in the stepped-wedged design (Figure 3). Simulation results showed that a power of 80% can be obtained under a relative risk reduction of approximately 22% in intrahospital perinatal deaths, which corresponds to a relative risk (RR) of 0.78. We expect this to be a realistic improvement target when considering concurrent reductions in stillbirths in Zanzibar’s tertiary hospital during the pre-post pilot study of PartoMa, where the majority of the decrease was among intra-hospital stillbirths (overall stillbirth rate fell from 59 to 39 per 1000 total births, RR 0.66; 95% CI 0.53–0.82) [24]. (Supplementary file S1).

Notably, potential declines in facility-births are reflected in these power calculations.

### Data analyses

Overall analyses of the situational findings, co-creation, and implementation processes and effectiveness rely heavily on mixed-methods evaluation. This will include a broad spectrum of designs, from sequential explanatory and exploratory methods to embedded and converging triangulation designs [61].

Concerning the quantitative components, descriptive analyses will be performed in all five facilities as cluster-units of analysis. QoC provision and experience indicators (pre-selected, non-ambiguous criteria) and birth outcomes will be analysed and compared both within and between facilities using mixed effects logistic regression. Differences in seminar attendance and seminar return rates between maternity units will be compared using logistic regression. Knowledge scores are modelled as longitudinal data and compared over time using linear mixed-effects regression. Effects on each outcome will be reported as an average effect across facilities and its significance will be determined by likelihood ratio tests. Possible differences in effect between facilities will be investigated by incorporating a random slope regression model, reported by its standard deviation along with facility-specific deviations from the total effect. Possible time-dependence of the intervention (e.g. delayed entry) is investigated by allowing its effect to depend on facility-specific time since implementation and by adjusting for seasonality patterns. Additional adjustments for covariates will also be performed, such as for staff and patient counts, availability of essential supplies, other competing interventions or unintended events in the facilities, national holidays, maternal characteristics, and referral patterns. Both unadjusted and adjusted results will be reported. A biostatistician in the study team will closely supervise statistical analyses. All summary statistics and effect sizes will be reported along with 95% Wald-based confidence intervals, and statistical significance will be set at 5% level.

The qualitative analysis plan is presented separately [32].

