#### III. Intervention implementation and evaluation

The overall implementation design will be a pragmatic stepped-wedged cluster-randomised trial with the five maternity units divided into three clusters receiving the intervention at cluster-level [50]. In a random order generated by R (R Core Team, 2017), maternity units will receive the intervention in three-month intervals. After enrolling in the third cluster, the intervention and evaluation will continue for additional nine months in all five sites (Figure 3).

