**Table ut0001:** 

**Box 1** The PartoMa pilot intervention in Zanzibar, consisting of pocket booklets with locally co-created guidelines on common care during birth and associated quarterly recurring seminars, where the guidelines are practiced in groups passing through five stations. In Zanzibar’s tertiary hospital, a pre-post study suggested that the multifaceted PartoMa intervention appeared associated with a 33% decrease in stillbirths and halving in babies with low Apgar score. The intervention follows a ‘self-directed approach’ where use of the guidelines and participation in seminars are voluntary and based on inner motivation. At each seminar station, locally realistic case stories are discussed, based on partographs and both routine and emergency care during birth, respectful support, triage, and hands-on training are included. The Zanzibar PartoMa guidelines are available online (publichealth.ku.dk/partoma). *Photos by [name], [name] and [name]. All identifiable people have given their oral consent*.

Finally, a challenge arises if the success of the implementation is highly different across sites, which may leave the overall results of the stepped-wedged trial inconclusive. In this case, the theory-based, mixed-methods study design will allow us to conduct in-depth analyses focused on individual effects at hospital level, which can be compared across sites. This flexibility to assess intra- and inter-site variability is particularly important for addressing questions of transferability and scalability. In addition, while the current evaluation timeframe reflects our funding limitations, it may be argued that an evaluation time frame of nine to 15 months is insufficient for assessing potential long-term impact. If the intervention appears effective and continues, we aim to fundraising for additional post-exit evaluations, including in-depth exploration of long-term sustainability and potential further scale-up in Dar es Salaam and beyond.

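### With five facilities, the planned random-slope SD, facility deviations and Wald intervals can understate differences in effect between sites; fixed facility-by-intervention effects should be reported beside them

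*Protocol article*

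**What the plan says.** Section III (Intervention implementation and evaluation) describes a "pragmatic stepped-wedged cluster-randomised trial with the five maternity units divided into three clusters". Under Data analyses, "birth outcomes will be analysed and compared both within and between facilities using mixed effects logistic regression". The average effect across facilities is reported and "its significance will be determined by likelihood ratio tests". Differences in effect between facilities are to be "investigated by incorporating a random slope regression model, reported by its standard deviation along with facility-specific deviations from the total effect". The same paragraph sets the interval rule: "All summary statistics and effect sizes will be reported along with 95% Wald-based confidence intervals". It names no exception for variance components or predicted deviations.

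The closing paragraph of Key Methodological Strengths and Limitations considers what happens if implementation succeeds very unevenly. The authors would then turn to hospital-level effects compared across sites, and they write: "This flexibility to assess intra- and inter-site variability is particularly important for addressing questions of transferability and scalability". No estimator is named for those hospital-level effects.

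**The concern.** Five facilities give four degrees of freedom for a variance. Maximum likelihood, the usual fit for a mixed logistic model, pulls such a variance towards zero and often places it on the boundary. Facility deviations predicted from the model are shrunken by the same estimate, so a zero SD makes all five deviations zero. A Wald interval for an SD at or near zero is not valid, and Wald-type intervals for the deviations treat the estimated SD as known.

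The random slope is the only heterogeneity output that the article names, and it can err towards similarity. Site variation is plausible here: the units mix regional referral and district hospitals, uptake is voluntary, and implementation may vary between sites. A zero or small SD could be read as a uniform effect when five sites simply could not show otherwise.

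**Working it through.** **Inputs from the article.** Five facilities in three randomised steps; three-month steps; 18 months of data, so six blocks; about 60,000 births a year, so 60,000/5/4 = 3,000 per facility-block; 80% power at RR 0.78; 5% level (two-sided assumed).

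**Assumed, because the article does not give them.** Deaths per facility-block; the true between-facility SD of the log effect (0.10 to 0.40); a 2/2/1 split of facilities over the three steps; random-intercept SD 0.3; fitting by maximum likelihood (ML).

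**1. The plan's own figure.** The article states "Simulation results showed that a power of 80% can be obtained under a relative risk reduction of approximately 22% in intrahospital perinatal deaths". This cannot be reproduced forwards, because the death counts are not in the article, which points to Supplementary file S1. It can be inverted. ln 0.78 = -0.2485, so the required SE is 0.2485/2.802 = 0.0887. Without calendar-period effects, a facility with c control and t intervention blocks, and d deaths per control block, contributes information d × 0.78ct/(c + 0.78t). That is 0.796d for (1,5), 1.219d for (2,4) and 1.315d for (3,3). The total is 2(0.796) + 2(1.219) + 1.315 = 5.345d, so d = 1/(5.345 × 0.0887²) ≈ 24. The same weighted least squares with period effects gives about 95. The simulations used 24 and 97, which at 3,000 births is 8 and 32 deaths per 1,000.

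**2. Floor set by five facilities alone.** With unlimited births, the ML variance behaves as τ² × χ²₄/5, with mean 0.8τ². The chance that the SD is below half the truth is P(χ²₄ < 1.25) = 1 - 1.625e^(-0.625) = 13%. For REML it is P(χ²₄ < 1) = 1 - 1.5e^(-0.5) = 9%.

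**3. Simulation.** 500 trials per setting, normal approximation to the log-count mixed model, ML, Monte Carlo error about ±4 points. Each pair is 24 deaths without period effects / 97 deaths with them.

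| True SD | 95% of sites, RR | SD estimated as 0 | SD below half the truth | Detected by random-slope LRT | Coverage, facility deviations |
|---|---|---|---|---|---|
| 0.15 | 0.58-1.05 | 40% / 19% | 46% / 34% | 14% / 45% | 52% / 68% |
| 0.25 | 0.48-1.27 | 24% / 8% | 36% / 22% | 39% / 79% | 63% / 79% |
| 0.40 | 0.36-1.71 | 6% / 2% | 20% / 18% | 75% / 93% | 79% / 85% |

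The RR ranges are 0.78 × exp(±1.96 SD). At SD 0.10 the estimate is zero in 57% / 36%. Wald intervals for the SD itself cover 55-80% over SD 0.15-0.40, counting zero estimates as misses. REML helps but does not cure: zero in 34% / 13% at 0.15 and 16% / 5% at 0.25.

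**4. Other runs.** A separate simulation (300 trials per setting) gave zero in about 24-48% at SD 0.15, 11-21% at 0.25 and 2-5% at 0.40. A third (4,000 trials, 70.5 to 90 deaths per block) gave 23-27% at 0.15 and 12-16% at 0.20. The rounded ranges of 20-50% and 10-25% span these results.

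**5. Fixed facility-by-intervention terms.** Their intervals cover 93-96% in all scenarios. At SD 0.25 the 4-df test has power 46% / 83%, against 39% / 79% for the random-slope test. At 24 deaths without period effects the facility SEs are 1/√(24 × 0.796) = 0.23, 1/√(24 × 1.219) = 0.19 and 1/√(24 × 1.315) = 0.18. At 97 deaths with period effects, the same weighted least squares gives 0.11 to 0.15.

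**The case against.** The article does not name maximum likelihood, and it does not say in terms that the slope SD gets a Wald interval; that follows only from the word "All" in the general rule. Both points stand, and they are why the conclusion is conditional. They do not remove it, because REML also falls short, and the random slope, its SD and its deviations are stated choices rather than details left open.

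Site-level work is already foreseen. Outcomes are compared within and between facilities, and hospital-level effects are planned if sites differ greatly. This mitigates the concern. However, that fallback is prompted by seeing large differences, and it has no fixed estimator.

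The method does best where differences are large. With three sites at RR 0.65 and two at 1.0, the SD is zero in 17% of trials at 24 deaths but 1% at 97, with detection in 45% and 92%. This stands. Nor do fixed terms overcome having five sites: they repair the intervals but add little power, and unshrunken estimates show some spread even when effects are equal.

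Three stronger readings are tempting, and the documents support none of them:
- **That the trial will usually report no site variation.** At SD 0.15 and above, the estimate is non-zero in most trials.
- **That scalability conclusions will be drawn from a zero SD.** The article says it will compare quantitative and qualitative results between sites.
- **That the 80% power is overstated.** The article uses the random slope only to investigate differences, and whether the power simulation assumed one common RR cannot be seen, because the supplement is not shown.

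**Conclusion.** The concern holds for the heterogeneity analysis. With five facilities and ML fitting, small to moderate true differences are often estimated as zero or well below their size: a zero SD in roughly 20-50% of trials at a true SD of 0.15 and 10-25% at 0.25. At 0.40 a zero is uncommon (2-6%), although about one trial in five still reports less than half the true SD. Wald-type intervals for the deviations cover about 52-85% rather than 95% over SD 0.15-0.40.

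These sizes rest on assumed death counts (24 to 97 per facility-quarter, inverted from the plan's power statement), an assumed true SD, a 2/2/1 split and a normal approximation. For outcomes with many more events, the problem shrinks towards the five-facility floor of 9-13%. The likelihood ratio test of the average effect and the stated 80% power are untouched.

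**What to change.** Amend the heterogeneity sentence under Data analyses, or fix the same in the analysis plan:

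- Alongside the random slope, report the five facility-by-intervention effects as fixed interactions, each with its own 95% interval, and the 4-df test of heterogeneity. Name these as the hospital-level effects meant in the closing paragraph of Key Methodological Strengths and Limitations.
- If the random-slope SD is kept, give it a profile-likelihood interval so that its upper limit is visible, and exempt it from the general Wald rule.
- State that a zero SD or a non-significant heterogeneity test is not evidence of equal effects.

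The cost is a change of wording and a few extra model outputs, with no new data. The price is wide facility intervals. With SEs of about 0.11 to 0.23 on the log scale, each limit lies a factor of about 1.24 to 1.57 from the estimate (exp(1.96 × 0.11) and exp(1.96 × 0.23)). Power to detect heterogeneity barely improves, and the report should say so.
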